## Potential Risks and Benefits

### Potential Risks

This study is a randomised controlled trial that will compare treatment with a full course of sulfadoxine-pyrimethamine and azithromycin (SP/AZ) at enrolment between 14-26 weeks and at two further visits at least 4 weeks apart, to a single treatment course of SP and chloroquine at first antenatal visit, and SP and AZ placebo at two subsequent visits. All women will be provided with long-lasting insecticide treated nets (ITNs). AZ has not been used extensively in PNG, but has been widely used elsewhere in developed and developing countries for treatment of STIs without evidence of adverse effects. There is a long history of use of both SP and chloroquine in pregnancy, without documented toxicity.

All drug used are usually well tolerated, however mild side effects such as nausea, diarrhoea, abdominal pain, dizziness, itching or mild rashes may occur with any of the drugs used.

Participants and their fetuses and newborn children will be monitored for the occurrence of severe adverse events, including events possibly or probably due to the study medications, by the study physicians. Details of the adverse event protocols are found in Section 9.2

In order to evaluate the effect of the drug intervention on malaria infection, haemoglobin concentrations and pregnancy outcome, blood samples will be taken at enrolment (10 ml) and at subsequent treatment visits (finger prick- 250 ml) and at delivery (10 ml). For a subset of women, an additional 5 ml venous sample (instead of a finger prick) will be taken at 28-34 weeks, for studies of immune responses to *P. vivax* in pregnancy as part of the PregVax Consortium. For a subset of 200 participating women (and 50 non-pregnant community controls), we will collect a further blood sample (10 ml) at 3 months post partum, for studies of P Vivax immunology. At delivery heel prick blood sample will also be collected from each baby. Although remote, there is a small, finite risk of infection associated with finger prick and venous blood draws. However, the PNGIMR has conducted many studies involving routine finger prick and venous blood sampling from the study populations and based on our experience from these studies, very few if any study-related adverse events, as defined below, have occurred or been reported to us.

We do not expect that participants in this study will be at significant risk of adverse consequences in the short or long term due to the study or the interventions provided. On the contrary, in large studies of SP and (separately) of AZ, severe adverse events due to the medication have been reported only extremely rarely (<1 in 10,000 persons). Moreover, both drugs have been used extensively in pregnant women in 2nd and 3rd trimester.

Azithromycin can induce antibiotic resistance in some bacterial species, notably S. pneumoniae (pneumococcus). Nasal swabs will be used to monitor rates of carriage, and resistance, of pneumococci.

### Known and Potential Benefits

The present study has the potential to provide both direct benefits for the study participants and general benefits for populations in malaria endemic areas in the SW Pacific and SE Asia.

For participants:

- in the SP+AZ group we expect a 30% reduction in the prevalence of LBW, and a reduction in the prevalence of malaria infection at delivery, and of severe anaemia compared to SP/CQ treatment.
- In the SP/AZ group we expect to see a reduction in the prevalence of STIs at 28-34 weeks compared to the control group.
- we will provide treated bed nets to all women, which we suspect will decrease the existing burden of malaria by around 25% on their own.

For PNG

- if the intervention proves successful, IPTp with SP +AZ is very likely to be quickly adopted. In order to facilitate such an uptake of IPTp into national treatment policies, the study will liaise closely with national and provincial health authorities.

For the wider scientific community:

- to date IPTp has not been tested in areas with high levels of P vivax malaria, or in areas outside Africa. The results of our trial will thus be highly relevant not only for PNG, but also for other countries with reasonably high levels of non-falciparum malaria.
- Combining malaria and STI interventions in one package has significant potential advantages for reproductive health programmes. Reducing the infectious disease burden in pregnancy may improve mothers’ health, decrease stillbirths and improve pregnancy outcomes,
- This study will contribute importantly to our understanding of the burden and consequences of P vivax infection in pregnancy.
- The genetics study will contribute to a greater understanding of why some pregnancies fail, and how reproductive success may be an important factor shaping the human genome.

# Objectives

**This protocol describes a randomised clinical trial of three dose administration of SP/AZ compared to single dose SP plus chloroquine and two doses of placebo to prevent low birth weight and control malaria and STIs in women using ITNS Madang Province, Papua New Guinea.**

The primary **goals** of the project are to determine whether the administration of intermittent preventive treatment (IPT) with sulphadoxine-pyrimethamine (SP) together with Azithromycin delivered through antenatal services is effective in increasing birth weight and reducing malaria parasitemia, STIs and anaemia in pregnant women. Additional goals include evaluating the burden of malaria disease due to *P. vivax*, examining the influence of IPTp on the prevalence of resistance to SP and (in S pneumoniae) to AZ, studying the human genome in the context of pregnancy outcome, and measuring the influence of IPTp on the acquisition of pregnancy-specific malarial immunity. In women who have malaria infection, we will study the characteristics of the parasites infecting them. **A benefit in our study populations would be used to support a change in PNG national policy for prevention of malaria in pregnancy, and would provide important information for other countries in the region**.

## Objectives

The **primary** **objective** of this proposal is to determine whether the administration of IPTp with SP plus AZ results in a significant decrease in the proportion of infants born with LBW. Key secondary objectives will include increases in mean birth weight and reduction in the incidence of malaria parasitemia, anaemia and sexually transmitted infections in participating women. Together, these will determine whether SP/AZ causes significant improvements in maternal and child health. This will be the first evaluation of IPTp with SP AZ outside Africa and in a setting in which *P. vivax* infection is highly endemic.

In addition, the study will investigate if the intervention may lead to an increase in levels of drug resistance; and evaluate the effect of IPTp on the development of immunity to malaria.

**Secondary objectives** of the study include:

1. To compare mean birth weight of babies born to women on SP+AZ and controls.
2. To examine the effect of SP + AZ on prevalence of *P falciparum* at delivery in peripheral, placental and cord blood films and on placental histology, and at second visit by PCR only in peripheral blood films.
3. To compare maternal haemoglobin concentrations and anaemia prevalence and severity between groups
4. To investigate the prevalence and consequences (maternal haemoglobin, birth weight and placental pathology) of *P. vivax* infection in pregnancy
5. To compare the immune response to *P. vivax*  in pregnant and non-pregnant hosts
6. To determine the incidence of symptomatic malaria by passive case detection in each group.
7. To compare the proportion of women carrying azithromycin-sensitive sexually transmitted infections at second treatment visit between groups.
8. To document the incidence and severity of Adverse Events possibly or probably associated with study medications
9. To examine the prevalence of drug resistance markers in parasites infecting women in late pregnancy
10. To measure the prevalence and antibiotic sensitivity patterns of *S. pneumoniae* in nasopharyngeal swabs collected at delivery
11. To measure the impact of IPTp on development of immunity to malaria in pregnancy
12. To document maternal, perinatal and infant mortality rates in each group.
13. To collect maternal and child DNA to study the genetics of reproductive success, as part of a planned multinational consortium.
14. To study the characteristics of parasites infecting pregnant women, such as parasite gene and protein expression and adhesion phenotypes.

The primary objective will be assessed by measuring infant birth weight at delivery and comparing the proportion of infants with birth weight <2500 g between the two groups.

**Immunological, genetic and parasitological studies related to this project will be described in separate sub-protocols.**

## Outcome measures

The efficacy of IPTp (SP/AZ) will be assessed in relation to the following indicators:

**Primary Objective**

### Primary Outcome Measure

1. Proportion of infants with birth weight <2500 g.

### Secondary Outcome Measures

- 1. Prevalence of *P falciparum* at delivery in peripheral, placental and cord blood films and on placental histology, and at second visit by PCR only in peripheral blood films.
  2. Mean maternal hemoglobin concentration at delivery, and proportion of women anaemic (Hb < 11 g/dl).
  3. Prevalence (at enrolment, second treatment, and delivery) and consequences (maternal haemoglobin, birth weight and placental pathology) of *P. vivax* infection in pregnancy
  4. Incidence of symptomatic malaria during pregnancy
  5. Proportion of women carrying azithromycin-sensitive sexually transmitted infections at second treatment visit (28-34 weeks).
  6. Incidence of Adverse Events, including severe adverse events (SAEs), and AEs possibly or probably associated with study medications
  7. Prevalence of drug resistance markers in parasites infecting women in late pregnancy, particularly in the P falciparum and P vivax dihydrofolate reductase and dihydropteroate synthase enzymes, associated with SP resistance.
  8. Prevalence and antibiotic sensitivity patterns of *S. pneumoniae* in nasopharyngeal swabs collected at delivery
  9. Maternal, perinatal and infant mortality rates.
  10. Impact of IPTp on development of immunity to malaria in pregnancy
  11. Characteristics of parasites infecting pregnant women.

# Study Design

**The study design of this research project is a randomised placebo controlled single blinded trial in pregnant women enrolled between 14 and 26 weeks’ gestation.** All women participating in this study will be followed until 6 weeks post partum. Infant survival to 1 year of age will be documented.

The intervention consists of three treatment courses of SP (3 tablets: 1500/75 mg) + AZ (2 g/day for 2 days) administered at ANC booking (provided this is between 14 and 26 weeks’ gestation) and at 2 further antenatal visits at least 4 weeks apart. Recipients in the control arm will receive a treatment course of Sp and chloroquine at enrolment, followed by AZ and SP placebos at further treatment time points. All women will be provided with a long lasting insecticide treated bed net. A block randomisation procedure will be used to allocate women to respective control and intervention groups. Among study staff, only those dispensing drug will be aware of subjects’ treatment allocation. At enrolment and at delivery a 10 ml venous blood sample will be collected to determine prevalence of malarial infections and to measure haemoglobin levels, as well as to contribute plasma, serum and peripheral blood mononuclear cells (PBMCs) for immunological analyses. At each subsequent treatment visit a 250µl finger prick blood sample will be collected for retrospective identification of malaria infection status.

At enrolment all women will have blood taken to test for syphilis by RPR and TPHA test, and women with positive tests indicating active or latent syphilis will be treated with benzathine penicillin according to standard treatment guidelines. Women will be asked to self-collect a high vaginal swab, for molecular diagnosis of STIs. Consenting women will also undergo testing for HIV (provided routinely by Modilon Hospital), and infected women will be referred to a local treatment centre providing highly active antiretroviral therapy, for prevention of mother to child transmission, and to maintain health of infected women.

From blood samples collected the prevalence and density of infections will be determined by light microscopy and PCR.

A subset of women who can attend ultrasound clinics at Modilon Hospital will have up to 3 ultrasound scans, to establish gestational age, monitor fetal growth, and measure placental blood flow.

At other regular antenatal care visits women will not be actively followed for morbidity. However, women self reporting febrile illness will be immediately diagnosed by study staff and if required treated for malaria.

At the time of scheduled final treatment dose, women will have a high vaginal swab collected, and all women with symptoms of STIs (or a positive diagnosis by PCR) will be treated according to PNG Standard Treatment Guidelines for Syndromic Management of STIs.

During the entire study period a passive case detection system will be maintained at the participating hospital and health centres (HC) to determine the incidence of symptomatic malaria illness. Every participating woman who presents with a febrile illness or symptomatic anaemia will be clinically assessed and have venous blood (5 ml) taken for the determination of malaria infection (by Rapid Test, confirmed by microscopy and PCR) and Hb level.

The use of a relatively broad spectrum antibiotic for the prevention of malaria and STIs in pregnancy, raises the concern that this intervention my increase resistance in other important bacterial pathogens. Even though the dose given is significantly higher than that recommended for treatment of bacterial illnesses, we will be monitoring resistance level in pneumococci collect from nasal mucosa of a subset of women delivery. Pneumococci were selected as carriage rates are high, and they are easily collected and cultured.

Each participant will thus have up to 4 regular study contacts during gestation and 2 after delivery (6 weeks and 12 months) and will be asked to contribute 2 x 10 ml venous blood samples and 1 or 2 finger prick blood samples (250µl) (See Study Schedule, Appendix I). Additional blood samples will be collected at time of febrile illness during passive case detection.

The safety of all study participants will be assured by a specifically constituted data & safety monitoring board (DSMB), while the study integrity will be guaranteed by regular visits by an external clinical monitor.

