The study team Physician or a trained study team Nursing Officer will assess the woman for sign of chronic illness, symptomatic severe anaemia or permanent disabilities that would preclude her participation into the study. (See 5.2 for list of exclusion criteria). If a woman is excluded on health grounds, she will be referred to nearest health facility for treatment.

Every enrolled woman’s health (record) booklet (already owned, or provided at enrolment) will be clearly marked with a study identifier and study ID number. At any study contact, the study team will record all medically relevant data collected during their examination into the health booklet.

Digital photographs will be taken of participating women at enrolment, and a printed version will be kept in a secure file, for tracking of pregnant women who fail to attend appointments, and to ensure accurate identification of women if required

Following assessment the woman will receive the 1st IPTp treatment dose. The drugs will be dispensed in pre-randomised and pre-numbered Ziploc bags that contain all drugs for initial treatment. The first dose (SP and AZ or SP and chloroquine) will be dispensed directly by the study staff. Pack number, date and time of administration will be recorded on the enrolment forms. The tablets will be administered with water. The woman will then be instructed how to take subsequent AZ or chloroquine doses at home. The woman’s treatment allocation will be noted using randomly-generated codes. Treatment allocation will not be revealed to laboratory staff, and will be kept concealed to the maximum extent possible from other study staff (see 6.3.3.). Senior study investigators will be aware of treatment allocation; hence the study will be single blinded.

A thorough physical examination (including axillary temperature, measurement of Hb etc. will only be conducted on enrolled women who spontaneously report as ill to either the study team or the health centre staff. Women with a presumptive diagnosis of malaria will be tested on the spot for malaria infection using a rapid diagnostic test (RDT). If they have a positive RDT they will be treated with a full course of Coartem and their randomised IPTp treatment (drug or placebo) will be delayed for at least 4 weeks. For all women reported sick, detailed symptomatology, results of RDT and treatments given will be recorded on the ‘Morbidity Surveillance Form’.

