The health centre staff will be requested to screen pregnant women who are attending ANC or outpatient clinics in order to determine if they are study participants. Screening can be accomplished by checking for study symbol and ID numbers on the woman’s Helt Buk (Health Book) or by referring to the list of study participants that will be kept at the study clinics. In addition, women who are participating in the study will be requested to aid the health centres and study team by alerting their health care providers that they are study participants when independently seeking care at one of the participating health centres. After initial diagnosis health centre staff will refer study participants to the IMR morbidity surveillance staff for further clinical investigations and data collections.

1. Diagnosis & Treatment

All participants identified by health centre staff will be referred to the health centre based study nurse. The study nurse will take a medical history and fill in the Health Centre Surveillance form. In the case of participants diagnosed with presumptive malaria, s/he will take a finger prick blood sample to make blood smears, measure haemoglobin and confirm the presumptive diagnosis using on site with a rapid diagnostic test (RDT) or diagnostic microscopy.

Upon confirmation of diagnosis of malaria illness, the participant will be treated by the study nurse with antimalarials. All symptomatic episodes will be treated with the rescue medication (i.e. 3 day course of Coartem). In the case of a haemoglobin < 6.0 g/dl study staff will treat the woman according to PNG national guidelines with a full course of antimalarials, albendazole for hookworm control and iron infusion.

For women with negative RDT/bloodslide and/or Hb ≥6.0 g/dl the health centre staff will be advised to refine the diagnosis for other febrile illnesses and treat accordingly. All women with a diagnosis other than malaria and anaemia will be treated by the health centre /hospital staff.

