### Specimen Collection, Preparation, Handling and Shipping

#### Instructions for Specimen Preparation, Handling, and Storage

1. **Blood Collection**
   1. Finger prick bleeds

At the second and third (where applicable) treatment dose blood samples of approximately 250 μl will be collected from each woman participating in the Protocol. Additional samples will be taken from symptomatic individuals during passive morbidity surveillance. These blood samples will be obtained by the finger prick method.

These samples will provide adequate blood for the preparation of thin/thick blood smears to detect the presence of malaria parasites, type of malaria parasites, and level of parasitemia. A portion of the sample also will be archived in a K+EDTA microtainer for laboratory analyses (e.g. serum & DNA preparation, PCR/LDR-based diagnosis of malaria parasites).

- 1. Venous blood draws

In order to have sufficiently large samples for the detailed immunological measurements detailed in the supplementary protocol, venous blood draws are needed at enrolment and delivery. The volumes of the venous draws are limited to 10 ml. Cell mediated immunology will be studied in separately funded studies.

Drawing venous blood samples will be done by specially trained staff. We will use butterfly needles of 21 gauge and heparinized vacutainers. Residual blood in the tube attached to the butterfly needle will be used to measure haemoglobin levels and make blood smears.

Venepunctures will be performed on veins in the participants’ arms. Upon removal of the needled localized bleeding is efficiently stopped with a small pressure bandage (e.g. a Band Aid). Properly done this procedure is virtually painless. However, if the needle punctures the blood vessel, there is a risk of local bleeding that can result in minor hematoma. In order to assure the safety of participants, they will be monitored following blood draw until it can be ascertained the local bleeding has stopped. Subjects will be instructed to present to the study nurses based at participating health centres in case of localized hematomas or infection at site of needle injection who will then attend to them and if necessary refer them for further treatment.

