**PCR**

In addition, we will also determine the presence of malaria parasites using PCR-LDR typing (see 6.2.1.2 a). This method has a higher sensitivity than light microscopy and it is therefore common to find infections that are detectable by PCR-LDR, but not by microscopy. Samples will be considered positive for any infections if the mean fluorescent intensity exceed a species specific threshold defined by the mean + 2 SD of negative controls.

Histology

Placental biopsies will be collected at delivery, fixed in 10% neutral buffered formalin,and paraffin embedded. Sections cut onto glass slides will be examined following staining with Giemsa and haematoxylin and eosin. Placentas will be classified as (a) active infection (presence of any parasitised erythrocytes) (b) past infection (presence of malaria pigment haemozoin, in fibrin deposits or in mononuclear leukocytes) and (c) no infection. Active infection will be further divided into active acute (presence of parasites, but not of haemozoin deposits) and active chronic (parasites, and malaria pigment in leukocytes or in fibrin deposits).

Maternal haemoglobin concentration

Measurement of haemoglobin by Hemocue cuvette will be used. Anaemia will be defined as Hb <11.0 g/dl, moderate anaemia as Hb 6.0-8.9 g/dl, and severe anaemia as Hb <6.0 g/dl.

Symptomatic Plasmodium Infection

For diagnostic purposes, a symptomatic Plasmodium infection is defined as any type of Plasmodium parasitemia observed by blood smear and/or a positive rapid diagnostic test, plus an axillary temperature ≥ 37.5° C or a history of febrile illness in last 48 hours.

This definition will be used for analysis of the secondary outcome of symptomatic malaria in pregnancy.

However, for analytical purposes we will use two additional definitions for symptomatic Plasmodium infections: a) any type of Plasmodium parasitemia observed by blood smear and/or PCR/LDR diagnostic assay, plus an axillary temperature ≥ 37.5° C or a history of febrile illness in last 48 hours b) a parasite density of > 1000/μl for *P. falciparum* and/or > 250/μl for non-falciparum, plus an axillary temperature ≥ 37.5° C or a history of febrile illness in last 48 hours.

Asymptomatic Blood-stage Plasmodium Infection

An asymptomatic blood-stage Plasmodium infection is defined as any type of Plasmodium parasitemia observed by blood smear or PCR-LDR confirmation with an axillary temperature less than 37.5° C and no history of febrile illness in last 48 hours.

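### Sections 4, 6.1.7 and 6.2.3 disagree on which women are tested in clinic-hours passive surveillance, so symptomatic malaria, a secondary outcome, may be under-counted

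*Combined protocol and SAP*

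**What the plan says.** **Section 4, Study Design.** The trigger is broad: "Every participating woman who presents with a febrile illness or symptomatic anaemia will be clinically assessed and have venous blood (5 ml) taken". The blood is "for the determination of malaria infection (by Rapid Test, confirmed by microscopy and PCR) and Hb level".

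**Section 6.1.7, Passive Surveillance (Diagnosis & Treatment).** The order of events is "After initial diagnosis health centre staff will refer study participants to the IMR morbidity surveillance staff". The study nurse takes a history and fills in a surveillance form for every referred participant, but sampling carries a condition: "In the case of participants diagnosed with presumptive malaria, s/he will take a finger prick blood sample to make blood smears, measure haemoglobin". The nurse is then to "confirm the presumptive diagnosis using on site with a rapid diagnostic test (RDT) or diagnostic microscopy". PCR is not named in this step.

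**Section 6.1.7, after hours.** Health centre staff take slides and finger-prick samples and run rapid tests. No presumptive-malaria condition is stated.

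**Section 6.2.3, Finger prick bleeds.** Extra samples during passive surveillance come from symptomatic individuals, and "These blood samples will be obtained by the finger prick method".

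**Section 7.2, Treatment Visits.** Women who report illness at an antenatal visit are assessed on the spot for malaria or anaemia, with no presumptive step.

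**Outcome definition, section 11.1.1.** For the secondary outcome, "a symptomatic Plasmodium infection is defined as any type of Plasmodium parasitemia observed by blood smear and/or a positive rapid diagnostic test", together with an axillary temperature of at least 37.5°C or a history of fever in the last 48 hours. An additional analytical definition also accepts PCR. Section 8.1.2 takes the outcome from passive case detection at the participating facilities, and section 6.1 rules out active detection.

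**The concern.** A case needs two things: fever (measured or reported) and a positive test. Section 4 tests on fever or symptomatic anaemia. The clinic-hours text of 6.1.7 tests on a clinician's label, and neither 11.1.1 nor Appendix II says what presumptive malaria means. If the label is the operating rule, a febrile woman first thought to have something else gives no slide, rapid test or PCR sample for that episode. She then counts as a non-case under every definition in 11.1.1, and no later analysis can recover her.

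The haemoglobin measurement in 6.1.7 sits behind the same condition. A woman with symptomatic anaemia and no malaria label may therefore have no study haemoglobin at that presentation, although section 9.3.2 makes symptomatic anaemia below 6 g/dl a reportable serious adverse event.

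At stake is the between-group comparison of symptomatic malaria incidence. Seven field sites could each apply the undefined term differently. The issue here is who is tested, not which test result counts as a case.

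**Working it through.** **1. The texts side by side.**

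| Source | Who is sampled | Specimen | Tests |
|---|---|---|---|
| Section 4 | Any febrile illness or symptomatic anaemia | 5 ml venous | Rapid test, confirmed by microscopy and PCR; Hb |
| 6.1.7, clinic hours | Diagnosed with presumptive malaria | Finger prick | Smears; rapid test or microscopy; Hb |
| 6.1.7, after hours | No condition stated | Finger prick | Slides, rapid test |
| 6.2.3 | Symptomatic individuals | Finger prick | Smears; remainder archived for laboratory work, including PCR |
| 7.2 | Women reporting illness at antenatal visits | Not stated | Assessed for malaria or anaemia |

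Sections 4, 6.1.7 (clinic hours) and 6.2.3 cannot all be followed. They differ on trigger, specimen and tests.

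**2. Where the gap lies.** At scheduled treatment visits, section 6.1.4 has smears and archived blood taken from every woman, and 6.2.1 repeats this for smears at every study visit. The sentence "Women with a presumptive diagnosis of malaria will be tested on the spot for malaria infection using a rapid diagnostic test (RDT") governs only the immediate rapid test there. A febrile woman at such a visit still has a slide and can become a case. Section 6.1.4 also gives Hb to any enrolled woman who reports ill. After-hours testing carries no stated condition. What remains is outpatient presentation during clinic hours.

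**3. Size.** The plan gives no figure to reproduce: Table 3 in section 11.2 has no row for symptomatic malaria, and no incidence or power is stated. The following is illustration only.

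Inputs: 1163 women per arm (Table 3, the low birth weight row). Assumed and not in the documents: control risk of 5%, 10% or 20%, a 30% reduction, and a share *s* of true episodes tested, equal in both arms.

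Counted risks are p1 = p·s and p2 = 0.7·p·s. With se0 the pooled and se1 the unpooled standard error of the difference, power = Φ[(p1 − p2 − 1.96·se0)/se1].

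- p = 10%, s = 1: p1 = 0.100, p2 = 0.070, se0 = 0.01157, se1 = 0.01155; Φ(0.635) = 74%.
- p = 10%, s = 0.7: p1 = 0.070, p2 = 0.049, se0 = 0.00981, se1 = 0.00980; Φ(0.18) = 57%.

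| Assumed control risk | s = 1 | s = 0.7 | s = 0.5 |
|---|---|---|---|
| 5% | 43% | 32% | 24% |
| 10% | 74% | 57% | 43% |
| 20% | 97% | 88% | 74% |

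On the rate scale, losing a fraction q of cases equally widens the interval for the log rate ratio by 1/√(1 − q): q = 0.1 gives 1.05 and q = 0.4 gives 1.29. In every row the expected ratio stays at 0.7ps/ps = 0.70, so equal under-testing costs precision and does not bias the ratio.

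**4. If testing differed by arm.** Observed ratio = true ratio × (s in SP/AZ ÷ s in control). With 80% against 90%, a true 1.00 reads as 0.80/0.90 = 0.89 and a true 0.70 reads as 0.62. With the shares reversed, they read as 1.13 and 0.79. Nothing in the documents suggests either split.

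**The case against.** The strongest reply is that the gap may be small in practice. Presumptive malaria is undefined and could mean any fever in an area where section 2 names malaria the leading cause of outpatient attendance. Section 6.1.7 itself, after describing the test, advises staff to look for other febrile illnesses in women who test negative. That order suggests testing first and relabelling afterwards. Section 6.2.3 speaks of symptomatic individuals. This has force, and it is why the size is unknown. It does not settle the matter: the sampling condition is still written, an initial diagnosis still comes before referral, and women with symptomatic anaemia but no fever would fall outside it even on the generous reading.

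A reader might infer three stronger things that the documents do not support.

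- *That treatment visits share the same gap.* They largely do not, because smears and archived blood are routine there.
- *That women with symptomatic anaemia never get a study haemoglobin.* Sections 6.1.4 and 7.2 provide assessment for women who report ill at treatment and antenatal visits. The doubt concerns clinic-hours outpatient presentation.
- *That the comparison is biased in favour of SP/AZ.* Section 6.3.3 keeps hospital and health centre staff blinded, and they appear to make the first diagnosis. The first course is not placebo controlled and dispensing staff know the code, so differential testing is conceivable. The documents do not say that dispensing staff also do surveillance.

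It is also fair to say that the surveillance form and the nurse's history already capture every referred woman, so untested presentations could partly be traced.

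**Conclusion.** The contradiction stands for passive surveillance in clinic hours, on trigger, specimen and test set. If 6.1.7 is followed literally, some febrile women cannot become cases, and some women with symptomatic anaemia may have no study haemoglobin to support the section 9.3.2 report. If section 4 is followed, neither problem arises.

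The expected consequence is under-counting, lower precision and variation between sites in one secondary outcome whose power was never stated. The power losses shown rest on assumed incidence, effect and testing share, and indicate scale only. Bias by arm is possible but not shown. The primary low birth weight outcome is untouched. The point merits correction because a specimen not taken cannot be recovered later and the remedy is cheap.

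**What to change.** 1. Reconcile section 4, both parts of 6.1.7 (clinic hours and after hours), 6.2.3 and 7.2 to one trigger, one specimen type and one test set for outcome ascertainment. Define presumptive malaria if the term is kept.
2. For outcome measurement, take the research slide and archived PCR sample from every participant who meets the clinical half of the 11.1.1 definition (temperature of at least 37.5°C, or fever in the last 48 hours), whatever her first diagnosis. This is in line with section 4.
3. Add a field to the surveillance form for eligible women not sampled, with the reason. Report sampling rates by arm and by site alongside the incidence result.

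Which clinical testing and treatment rule applies, including haemoglobin testing and how results are used in care, is for the protocol team to reconcile.

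The cost is protocol wording, one form field and some additional slides and samples. Section 6.1.7 already sends every identified participant to the study nurse, so no new visit is needed.
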